Positive HIV-1 serology within a maximum of 24 weeks of a documented negative HIV-1 serology test result (can include point of care test (POCT) using blood for both tests). The estimated time of infection is taken as the midpoint between the dates of the negative HIV-1 serology or POCT test and positive HIV test at diagnosis, unless there was clear evidence for a transmission event, in which case that date will be taken.The date of a positive p24 antigen result and a negative HIV antibody test.The date of a negative HIV antibody test with either detectable HIV RNA or proviral DNA.Recent infection testing algorithm (RITA) reported as ‘Incident’ confirming the HIV-1 antibody avidity is consistent with recent infection (within the preceding 16 weeks). The estimated date of infection is assumed to be 2 months prior to the date of the incident test result.The date of a weakly reactive or equivocal 4th-generation HIV antibody antigen test.The date of an equivocal or reactive antibody test with less than 4 bands on western blot.Stable on ART with suppressed undetectable HIV viral load (VL) ‘target not detected’ using local assays for ≥1 year.No evidence of viral insensitivity to either 10-1074 or 3BNC117 antibodies based on proviral sequencing algorithm.Hepatitis B virus (HBV) surface antigen or HBV DNA, hepatitis C virus (HCV) Ag or HCV RNA negative or HCV anti-core antibody negative.No significant comorbidities.Nadir CD4 > 350 cells/μL.Current CD4 count > 500 cells/μL or CD4:CD8 ratio > 1.On integrase inhibitor (INSTI) or boosted protease inhibitor (bPI)-based regimen at time of randomisation, if previously on non-nucleoside reverse transcriptase inhibitor (NNRTI) has switched at least 4 weeks prior to randomisation.Adequate haemoglobin (≥120 g/L for males, ≥110 g/L for females).Weight ≥ 50 kg.Females capable of becoming pregnant must agree to use hormonal contraception, intrauterine device, intrauterine hormone-releasing system, or to complete abstinence from at least 2 weeks before the first bNAb/placebo infusion and for 20 months after the last bNAb infusion.Participants must have been vaccinated against coronavirus (COVID-19), at least 4 weeks prior to enrolment.

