#### Antiretroviral treatment interruption

Individuals on triple ART with suppressed HIV VL will be enrolled into the study and receive either dual bNAb or placebo, 3 days later they will then stop ART. The date of ART stop is considered time 0 for time to viral rebound estimation. At the time of recruitment, all participants will be receiving ART according to current best practice and the BHIVA guidelines [14]. At the time of randomisation, participants’ ART regimen must include an INSTI or bPI; if on an NNRTI, they must be switched to an INSTI or bPI at least 4 weeks prior to randomisation [16]. The ART regimen after viral rebound should ideally include an INSTI or bPI. Other changes in ART outside the protocol-mandated ART interruption period, and any other concomitant medical therapy either at screening or during the study will be recorded.

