### Strategies to improve adherence to interventions {11c}

#### Adherence to ART

ART treatment compliance will be the responsibility of each study participant and their routine HIV physician. Investigators will promote compliance by providing instruction for participants to take ART exactly as prescribed during the course of the trial. Participant compliance to ART or remaining off ART will be closely monitored throughout the trial through regular HIV viral load monitoring. Blood measurement of ART levels will be undertaken retrospectively to ensure that for evaluation of the primary endpoint individuals with controlled viraemia are not on any ART drugs.

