### Outcomes {12}

The primary endpoint is the comparison of time to viral rebound within 36 weeks after initial ATI, during Stage 1, summarised by hazard ratios.

Secondary endpoints, for both stages 1 and 2, are:
Safety defined as the number and types of adverse events (AEs) and serious adverse events (SAEs) by groupLength of time undetectable in days following ATI in the absence of detectable ART (comparing arm A vs B and arm B Stage 1 ATI vs Stage 2 ATI), summarised by mean.CD4 T cell counts and CD4:CD8 ratios at weeks 12-, 24-, 36-, and 48-week post randomisation, and 12-weekly until the end of study participation by arm, summarised by median.Percentage of participants with undetectable VL at week 12, 24, 36, and 48 post randomisation (Stage 1; arm A vs B) and then for arm B participants post second ATIQuantitation of proviral HIV DNA and cell-associated RNA at baseline and following viral rebound and resuppression on ART by arm.Duration of remission analysed under multiple alternate definitions (e.g. VL < 40 copies/mL, < 400 copies/mL, < 1000 mL), comparing arm A vs B and arm B Stage 1 ATI vs Stage 2 ATI, summarised by mean.Time to restarting ART after start of ATI, comparing arm A vs B and arm B Stage 1 ATI vs Stage 2 ATI, summarised by median.Time to undetectable HIV VL after restarting ART, comparing arm A vs B and arm B Stage 1 ATI vs Stage 2 ATI, summarised by median.The proportion of participants with detectable ART levels in blood during ATI, at weeks 12, 24, 36, and 48 post randomisation, by arm.bNAb concentration in blood at dosing, weeks 2, 4, 8, 12, 24, 36, and 48, time of viral rebound, and end of study, summarised by mean.Proportion and description of bNAb resistance/sensitivity at pre and post infusion time-points, by arm.Descriptive changes in reported HIV Quality of Life measures at baseline, 2 weeks after infusion, and at the end of study [21].

Tertiary or exploratory endpoints, for both stages 1 and 2, will include:
HIV-specific (humoral and cell-mediated) and innate immune responsesImmune phenotyping and activation/exhaustionHost gene expressionViral sequence and integration site analysisMeasures of the HIV viral reservoir in CD4+ T cells.

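### The ART-level test times run from randomisation, so they reach arm B's second interruption only incidentally, although the Stage 2 comparison depends on ART being absent then

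*Protocol article*

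**What the plan says.** Outcomes {12} in the protocol article introduces its list with "Secondary endpoints, for both stages 1 and 2, are". One item is the number of days undetectable after ATI with no ART detectable, compared between arms and between arm B's Stage 1 and Stage 2 ATIs. A later item gives the test times: "The proportion of participants with detectable ART levels in blood during ATI, at weeks 12, 24, 36, and 48 post randomisation, by arm". The item on the percentage with undetectable viral load adds a separate clause for arm B after the second ATI. The ART-level item has no such clause.

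The section Adherence to ART says that taking ART or staying off it is "closely monitored throughout the trial through regular HIV viral load monitoring". It then states what the drug assays are for: "Blood measurement of ART levels will be undertaken retrospectively to ensure that for evaluation of the primary endpoint individuals with controlled viraemia" are not taking ART. The primary endpoint belongs to Stage 1.

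On regimens, the section Antiretroviral treatment interruption says of the period before randomisation: "if on an NNRTI, they must be switched to an INSTI or bPI at least 4 weeks prior to randomisation". The inclusion criteria agree. For the period that leads to the second ATI, the same section says: "The ART regimen after viral rebound should ideally include an INSTI or bPI".

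**The concern.** A long second ATI without viraemia is the trial's evidence that control can outlast the antibody. That reading requires the participant to be off ART, and viral load cannot settle the matter, because ART and immune control both give an undetectable result. Only a drug assay separates them. The stated assay times follow a clock that suits the first ATI, and the stated purpose covers only Stage 1. ART missed in the second period would add undetectable days there and not in the first, and so would favour the hypothesis. The two paired periods are also entered under differently worded regimen conditions.

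**Working it through.** **The plan's own Stage 2 figure.** Inputs from Sample size {14}: SD 14 days, correlation 0.7, 36 patients, 15% dropout, 90% power, two-sided 5%.
- SD of the within-person difference = 14 × √(2 × (1 − 0.7)) = 10.84 days.
- Evaluable pairs = 36 × 0.85 = 30.6.
- The paired t-test detects 6.57 days at 30.6 pairs and 6.64 days at 30.

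The stated 6.6 days is reproduced. The point does not depend on it.

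**When the second ATI starts.** Trial design {8} gives the antibody at ART restart and then 24 weeks of washout. The section on PBMC and plasma samples gives the antibody one week after restart and the second ATI 24 weeks after that. The two statements differ by a week and should be reconciled; both are carried here. With restart at week r after randomisation, the second ATI starts at r + 24 or r + 25.

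**Which listed weeks can fall in it**

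| Listed week | Falls on or after the start of the second ATI if |
|---|---|
| 12, 24 | in practice never, because the start is at least week 24 plus the time to rebound |
| 36 | r ≤ 12 (or r ≤ 11) |
| 48 | r ≤ 24 (or r ≤ 23) |

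The greatest possible age of a listed test is 48 − 24 = 24 weeks into the second ATI. The same listed week also means different things for different people. With the 25-week interval, week 36 is 9 weeks into the second ATI for restart at week 2, and its first day for restart at week 11.

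**How many participants.** Sample size {14} assumes 90% placebo rebound by week 36. Two assumptions are added here: an exponential shape, and restart at rebound. Among those who rebound within 36 weeks, P(T ≤ t) = (1 − 10^(−t/36)) / 0.9.

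| | Start at r + 24 | Start at r + 25 |
|---|---|---|
| Started by week 36 | (1 − 0.464)/0.9 = 59.5% | (1 − 0.495)/0.9 = 56.1% |
| Started by week 48 | (1 − 0.215)/0.9 = 87.2% | (1 − 0.230)/0.9 = 85.6% |
| Two listed tests possible | 59.5% | 56.1% |
| One possible | 27.6% | 29.5% |
| None possible | 12.8% | 14.4% |

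Of 36 × 0.9 = 32.4 expected rebounders, 12.8-14.4% is about 4 to 5 people. Restart later than rebound, or rebound after week 36, lowers coverage.

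**Scale of possible bias.** With 30 pairs, the mean shifts by the total of falsely undetectable second-period days divided by 30. A shift of 6.6 days takes 6.6 × 30 = 198 such days in total, for example 66 days in each of three people. This is a break-even figure, not a forecast: the documents give no rate of undisclosed ART use. It should not be combined with the timing model either, because exponential rebound over 36 weeks implies a much wider spread than the 14-day SD.

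**The case against.** The strongest reply is that testing in the second ATI is already implied. The secondary endpoints apply to both stages, and the Stage 2 comparison has absence of ART in its definition. The per-protocol definition in Statistical methods {20a} removes anyone with ART found in blood during ATI and is not limited to Stage 1. The listed weeks may be reporting times rather than the whole assay schedule. Table 3, the Stage 2 schedule, is not shown, and the article condenses a fuller protocol. Research blood is drawn fortnightly while viral load is undetectable, so long controllers have many stored samples.

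Most of this stands. A reader might infer that ART in the second period goes unverified. The documents do not support that: they imply testing, and weeks 36 and 48 do reach many second ATIs. What remains is that the only stated times run on the wrong clock for this endpoint, and the only stated purpose is the primary endpoint. The per-protocol rule works only where an assay is done, and {20b} applies that set to some secondary outcomes only. Table 4 lists no ART-level assay among the research tests, so the stored blood shows that the remedy is feasible, not that it is planned.

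Two further readings go too far.
- One might count every second ATI that contains no listed test. If each second ATI lasted exactly as long as the first, a test would fall inside it only for T between 6 and 24 weeks: (0.681 − 0.215)/0.9 = 52%, leaving 48% without. But (1 − 0.681)/0.9 = 35 points of that are people who had already rebounded visibly before the next listed week, and their viraemia ends any claim of control.
- One might put a number of days on carry-over from an NNRTI-based regimen. The documents give no persistence data, no reason for the 4-week switch interval and no expected share on such a regimen. All participants enter on an INSTI or bPI regimen. No such figure can be supported.

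The two regimen statements govern different time points and so do not contradict each other outright. They do leave the paired periods under unequal stated conditions.

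**Conclusion.** The concern holds in limited form. The Stage 2 comparison requires ART to be absent in the second ATI, but the stated test times reach that period two, one or zero times depending on the week of restart, and never after its week 24. The timing limits follow from the document alone. The 13-14% with no possible listed test rests on exponential rebound and restart at rebound. The direction of any bias is clear; its size cannot be derived from the documents. The regimen wording is a secondary issue of comparability between the paired periods. Only secondary Stage 2 comparisons are affected. The Stage 1 primary endpoint and both sample sizes are untouched.

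**What to change.** 1. In Outcomes {12}, state the ART-level times from the start of each ATI, for example weeks 12, 24, 36 and 48 of each, plus the last undetectable sample. The last item matters because an ATI shorter than 12 weeks has no week 12 test on either clock.
2. In Adherence to ART, extend the retrospective assays to the Stage 2 time-undetectable endpoint.
3. Run the assays on blood already scheduled under Exploratory / research samples and under PBMC and plasma samples.
4. Reconcile the two regimen statements for the paired comparison. No view is taken here on which is right. If they stay different, prespecify a sensitivity analysis by the recorded regimen before each ATI.

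The cost is a few lines of wording and assays for at most 36 people. A few pairs may drop out of the sensitivity set.

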### Participant timeline {13}

The study visit schedules are summarised in Tables 2 and 3.

**Table 2 Tab2:**
[figure not shown]
Trial assessment schedule for Stage 1 (both arms A and B)

1. Visit prefix nomenclature: Screening ‘S’; During ATI ‘A’; After Rebound ‘B’ After Second Rebound ‘C’

1. Screening and Enrolment visit may be combined into one visit where possible

2. 4-weekly visits repeated until viral rebound occurs

3. UNS: patients may request an additional ‘unscheduled’ visit to have HIV VL measured any time while still unsuppressed

4. bNAb sensitivity visit at screening not required if done as part of the HEATHER study

5. Arm B/Placebo participants (if they agree) will move to Stage 2 after viral rebound to continue with the study visits, B1 visit procedure will be conducted as per Stage 2 schedule, otherwise participants will follow Stage 1 visit schedule until the end of the study

6. ^#^SARS-Cov-2 PCR will be conducted up to 72 h prior to randomisation/dosing visit and for the rest of the visits PCR will only be performed if participants exhibit COVID-19 (SARS-Cov-2) symptoms, however SARS-CoV-2 PCR testing can be offered to any asymptomatic participant attending at any study visit in accordance with local NHS guidelines, and participant or clinical team choice.

7. ATI Start visit (A2) can be conducted as an onsite or telephone visit if participant prefers

8. Arm B: Research bloods can be taken at the viral rebound visit or the Stage 2 dosing visit – not both visits.

9. SARS-Cov-2 antibodies blood test at screening is an optional test and is not used to determine if the patient is eligible for the study

**Table 3 Tab3:**
[figure not shown]
Trial assessment schedule for Stage 2 (arm B only)

1. Visit prefix nomenclature: Screening ‘S’; During TI ‘A’; After First Rebound ‘B’; After Second Rebound ‘C’

2. 4-weekly visits repeated until viral rebound occurs

3. UNS: patients may request an additional ‘unscheduled’ visit to have HIV VL measured any time while still unsuppressed

4. ^#^SARS-Cov-2 PCR will be conducted up to 72 h prior to ATI visit (B20) and for the rest of the visits PCR will only be performed if participants exhibit COVID-19 (SARS-Cov-2) symptoms

5. Visit B1 can be conducted as an onsite or telephone visit for arm B participants. The safety bloods and physical examination can be conducted at the confirmatory viral rebound visit if participant chooses B1 to be a telephone visit.

6. Research bloods can be taken at the dosing visit or the viral rebound visit at Stage 1—not at both visits

7. Visits B11-19 can be 4-weekly visits if participant has had two previous undetectable viral load while on ART

### Sample size {14}

#### Sample size and power considerations

Stage 1—arm A compared to arm B

Underlying viral rebound rates at 36 weeks of 90% and 55% in the control and intervention groups respectively (i.e. 10% and 45% free from rebound by 36 weeks; hazard ratio 0.35) will be detected with 90% power using a two-sided log-rank test at the 5% significance level provided there are 31 participants per arm and no loss to follow-up or return to ART treatment prior to 36-week primary outcome. We propose to recruit 72 participants in order to provide an allowance of approximately 10% return to ART treatment, and loss to follow-up, prior to the earlier of either 36 weeks or a primary event.

Stage 2—arm B only

For patients in arm B, we will look at the within-person difference in ‘length of time undetectable (in days)’ between first and second period. Assuming a standard deviation of 14 days and a conservative correlation between the number of days in the first and second period of 0.7, 36 patients will allow detecting a difference of 6.6 days between the two periods with 90% power and two-sided alpha 0.05, including 15% dropout rate.

### Recruitment {15}

The study population comprises participants with confirmed primary HIV infection who started ART within 6 months of confirmed primary HIV infection, and who have remained on suppressive ART without interruption for at least 12 months. The HEATHER study provides a pre-existing cohort of participants whom will be invited to participate if eligible. In addition, interested participants otherwise eligible but not enrolled into the HEATHER cohort may also be enrolled.

Eligible consenting participants who have not previously been enrolled into the HEATHER study, but fulfil the RIO eligibility criteria, may also be included and clinicians from participating clinical sites will be asked to identify and discuss their potential participation to the RIO trial. Interested and eligible participants will be referred to research staff at the clinical site for recruitment.

A website was created for RIO, this will include information on the eligibility criteria and participants are able to contact trial staff if interested to take part in the study (https://riotrial.org/)

## Assignment of interventions: allocation

### Sequence generation {16a}

Randomisation and unblinding will be carried out using a web-based randomisation and Electronic Data Capture (EDC) system, called Openclinica. Randomisation will not be stratified but will be blocked to ensure equal allocation to each arm.

Stage 2 will be unblinded.

### Concealment mechanism {16b}

The study will initially be double-blinded to study arm. Participants will be randomly allocated to initial treatment with bNAbs or placebo control then subsequent bNAb in a 1:1 ratio. Participants will receive blinded, identical-looking infusions at the initial dosing visit. The second infusion visit for arm B will be unblinded.

Each participant will be assigned a unique trial ID which is linked to the treatment allocation for Stages 1 and 2 of the trial. With the exception of planned unblinding prior to commencing the second infusion in arm B, the treatment code must not be broken. Exceptions include medical emergencies when the appropriate management of the participant necessitates knowledge of the treatment, or if expedited reporting of an unexpected and related SAE to the Research Ethics Committee (REC) and Medicines and Healthcare products Regulatory Agency (MHRA) is required.

### Implementation {16c}

The research team at each clinical site responsible for the enrolment of participants and follow-up procedures except the administration of IMP or placebo will be blinded to study arm.

The study monitor and ICRF team (pharmacist, nurses, and doctors) will be the only people unblinded to study arm. They will be responsible for storing, dispensing, preparing, and delivering the infusion and placebo at the randomisation visit and will allocate and administer the IMP or placebo to participants.

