### Intervention description {11a}

#### Investigational Medicinal Products (IMP) - bNAbs

The RIO trial involves administration of two bNAbs: 10-1074-LS and 3BNC117-LS, and placebo infusions (0.9% sodium chloride solution). 3BNC117-LS is a recombinant, fully human monoclonal antibody (mAb) of the IgG1κ isotype that specifically binds to the CD4 binding site (CD4bs) within HIV-1 envelope gp-120.

10-1074-LS is a recombinant, fully monoclonal antibody of the IgG1λ isotype that specifically binds to the base of the V3 loop within the HIV external membrane glycoprotein, gp120.

The original antibodies 3BNC117 and 10-1074 were identified and cloned at the Rockefeller University from an HIV-positive individual. Both 3BNC117-LS and 10-1074-LS differ from the original parental antibodies by two amino acid substitutions which were introduced for the purpose of extending their biological half-life.

Placebo arm B will receive 0.9% sodium chloride (normal saline) infusion identical in appearance and volume to the bNAb infusions.

Investigator brochures (IB) for 10-1074-LS and 3BNC117-LS IB will be used in the trial.

Both bNAbs will be stored at 5 ± 3 °C, and each bNAb vial contains a nominal 150 mg/ml of bNAb protein in a 1.0-mL buffered solution.

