## Assignment of interventions: Blinding

### Who will be blinded {17a}

Apart from ICRF research staff who will administer either the IMP or placebo, all trial participants, care providers, outcomes assessors, and data analysts will be blinded to the study arm allocation of each participant for the duration of Stage 1 of the trial.

ICRF research staff will be blinded to outcomes collection and analysis.

The Independent Data Monitoring Committee (IDMC) and study statistician preparing the IDMC report will require access to fully unblinded data.

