Immunological symptoms listed below are possible with administration of a monoclonal antibody and will be considered AEs of interest. Potential allergic-type reactions during and immediately following the administration of 10-1074-LS and 3BNC117-LS will be carefully monitored.
Constitutional symptoms, e.g. fever, change in blood pressure, rigours/chills.Injection site reactions/extravasation changes, pruritis, urticaria, erythema, desquamation, ulceration.Serum sickness like syndromes as evidenced by fever, rash, arthralgia, arthritis, nephritis.Deposition of immune complexes in the kidneys leading to renal insufficiency.Anaphylaxis; adult respiratory distress syndrome, bronchospasm, or wheezingCytokine release syndrome

Suspected unexpected serious adverse reactions (SUSARs) are defined as a SAR judged related to any dose of study drug administered, and not consistent with the applicable to the product information as set out in the IB for the investigational medicinal products. SUSARs should be notified to the appropriate regulatory authority, relevant REC, and the sponsor in accordance with regulatory requirements. SUSARs which are fatal or life-threatening will be reported not later than 7 days after becoming aware of the SAE. Any additional relevant information will be sent within 8 days of the report. Other non-fatal or life-threatening SUSAR will be reported within 15 days. Follow-up of participants who have experienced a SUSAR should continue until recovery is complete or the condition has stabilised. SUSAR reports should be unblinded prior to submission if required by national regulatory requirements.

Annual safety reports will be submitted to the sponsor, the ethics committee, and regulatory authority in accordance with regulatory requirements.

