### Potential risks of the study

#### Risk of the intervention (bNAbs)

The use of bNAb infusions is experimental with, at time of writing, an estimated 27 (including 6 HIV-positive individuals) and 43 (including 15 HIV-positive individuals) study participants having received 10-1074-LS and 3BNV117-LS respectively. In total, 40 participants (including 5 HIV-positive individuals) have received both antibodies simultaneously in studies that had stopped recruitment or completed [28]. Studies with either bNAbs are ongoing (Table 1) and more data will be available on an ongoing basis.

As with all antibody infusions, there is a risk of anaphylaxis to the protein, and close monitoring will be necessary within a Clinical Research Facility. This requires well-trained clinical staff, access to intensive medical support if necessary, and monitored review of the participant both before, during, and at least an hour after completion of the infusion. To date, there have been no reported cases of anaphylaxis to either of the bNAbs included in the study [[name] personal communication]. Mild local and systemic reactions may be observed, and participants will have a weekly medical review including regular health screening questions, for the first 8 weeks after receipt of the infusions, and subsequently twice monthly. Infusion of antibodies carries a potential risk of thromboembolism, and coagulation screening tests will be performed at screening. Individuals at increased risk of thromboembolic disease will not be eligible for inclusion in the study.

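### Acute infusion reactions at the Stage 1 dosing visit are first observed by nurses and doctors who know the arm, although the infusions look alike and adverse events by arm are a secondary endpoint

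*Protocol article*

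**What the plan says.** Only the protocol article is available. It sets out blinding in two places.

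- Implementation {16c}: "The study monitor and ICRF team (pharmacist, nurses, and doctors) will be the only people unblinded to study arm". This team stores, prepares and delivers the product and "will allocate and administer the IMP or placebo to participants". The research team at each clinical site is "responsible for the enrolment of participants and follow-up procedures except the administration of IMP or placebo will be blinded to study arm".
- Who will be blinded {17a}: "all trial participants, care providers, outcomes assessors, and data analysts will be blinded to the study arm allocation of each participant" for Stage 1. The same sentence opens with an exception for the ICRF staff who give the infusion. The next sentence adds: "ICRF research staff will be blinded to outcomes collection and analysis".

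On the infusions, the Investigational Medicinal Products text under {11a} describes the placebo as a saline "infusion identical in appearance and volume to the bNAb infusions". Concealment mechanism {16b} also says that the initial infusions look identical.

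On reactions, Adverse event reporting and harms {22} lists the events of interest after a monoclonal antibody and says: "Potential allergic-type reactions during and immediately following the administration of 10-1074-LS and 3BNC117-LS will be carefully monitored". The Discussion, under Risk of the intervention (bNAbs), requires close monitoring in a clinical research facility, with "monitored review of the participant both before, during, and at least an hour after completion of the infusion". Study setting {9} places every infusion visit at the ICRF.

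**The concern.** The reactions most directly tied to an antibody infusion occur while it is running or soon after. Several of them, such as chills, itching, flushing or mild wheeze, depend on someone noticing them and judging that they deserve a note. An observer who knows that a participant received saline may look less closely or explain a symptom away. An observer who knows that it was antibody may do the reverse.

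Safety by group is a secondary endpoint (Outcomes {12}), reported as proportions and rates within and between arms with 95% confidence intervals (Statistical methods {20a}). One purpose of a matched placebo is to make that comparison fair for infusion reactions. Telling the bedside clinicians the allocation gives up part of that benefit, and no reason is stated.

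**Working it through.** No figure in the document bears on this point, so there is no calculation to reproduce. The check sets the sections side by side.

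1. **Who is present at dosing?** All infusions take place at the ICRF ({9}), and its team gives them ({16c}).
2. **What do they know?** The whole team is unblinded, and nurses and doctors are named alongside the pharmacist ({16c}). {17a} confirms this by excepting the administering staff.
3. **What do they have to judge?** They watch for reactions before, during and for at least an hour after the infusion (Discussion). Under {11b} the infusion rate may be changed for an adverse reaction, and the infusion halted if the reaction persists. Those giving the infusion must therefore recognise reactions and act on them, whoever later completes the form.
4. **For how long?** Each antibody runs for about 30 minutes as a separate infusion. Assuming that the two run one after the other, and that placebo is timed in the same way, the window is 2 × 30 minutes plus at least 60 minutes, or about two hours or more per participant.
5. **How many visits?** 36 + 36 = 72 planned Stage 1 dosing visits, all under the same rule.
6. **Can a blinded person see the same signs later?** Only in part. The ATI start visit follows the infusion by 2 or 3 days (the article gives both) and may be held by telephone (notes to Table 2). A brief blood pressure change or wheeze will have gone by then. A blinded site team would rely on the participant's recall or on notes made by unblinded staff.
7. **Does the separation in {17a} settle it?** Not as written. If ICRF staff contribute to the record of dosing-day reactions, they take part in collecting a secondary outcome, and the statement that they are kept from outcome collection is not met. If they do not, the article names nobody else who is present to assess these reactions. {22} gives causality to the trial physician without saying whether that person could be one of the unblinded doctors.
8. **Is bedside unblinding needed?** Nothing in the article shows that it is. The infusions match in appearance and volume, emergency unblinding is available through the data capture system ({17b}), and {23} already assigns product supply and pharmacy matters to a separate unblinded monitor.

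**The case against.** The strongest reply is that {17a} is open about the arrangement. It excepts the administering staff in the same sentence that blinds outcome assessors, then separates those staff from outcome collection. {16c} gives follow-up to blinded site teams. No section says that ICRF nurses or doctors record, grade or attribute adverse events; that detail would normally be in the full protocol, the eCRF manual or the safety reporting instructions. Participants are blinded too and can report dosing-day symptoms at the blinded weekly reviews that run for the first 8 weeks. Some signs, such as temperature and blood pressure, are measured.

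Much of this stands, and it rules out stronger readings that a reader might infer:

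- **That {16c} and {17a} flatly contradict each other.** They do not. Both leave ICRF dosing staff unblinded and site teams blinded.
- **That adverse events of interest are recorded with knowledge of arm.** The text supports only that acute reactions are first observed by people who know the arm. Recording and attribution by them is an inference.
- **That all events of interest are exposed.** Serum-sickness-like syndromes and renal immune-complex deposition would be expected to emerge during follow-up by blinded teams.
- **That assignments already seen in the blocked list could influence enrolment.** Blinded sites enrol participants and randomisation is web-based, so no route to selection bias is shown.

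What the reply does not answer is the choice itself. The article does more than leave a detail open: it states that bedside nurses and doctors are unblinded, which is wider than a matched placebo requires. Later participant reports cannot fully replace observation in real time, and disclosing an exception does not remove the bias that it allows.

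**Conclusion.** The concern holds for acute reactions at the Stage 1 dosing visit. Unblinded clinicians make the first observation of these events at all 72 planned visits, and the events feed a secondary endpoint compared between arms. The between-arm comparison of acute infusion reactions is therefore open to avoidable observer bias.

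The size of that bias cannot be derived. The article gives neither an expected reaction rate nor any basis for how far recording might differ by arm, so a figure in percentage points would only restate assumed inputs.

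The primary endpoint is not affected by this point: it rests on laboratory viral load, with adjudication blinded to arm. Stage 2 is open-label by design and is also outside it. The conclusion assumes that the blinding rules in the article are those being followed; if the full protocol already places a blinded assessor at the bedside, only the article's wording needs correcting.

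**What to change.** - In {16c} and {17a}, limit routine Stage 1 unblinding at the ICRF to the pharmacist or other staff who prepare the product. Specify that the unblinded monitor is the supply and pharmacy monitor described in {23}.
- Keep blinded the ICRF nurses and doctors who give the infusion and who observe, record or attribute dosing-day reactions. The emergency unblinding route in {17b} remains available to them.
- Reconcile {16c}, {17a}, {22} and the Discussion on who assesses dosing-day reactions, and state whether the trial physician who assigns causality is blinded.

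The cost is modest but not nil. Preparation has to be separated from bedside administration, which {16c} now gives to one team, and the delegation log must reflect the split. Bedside staff who need the allocation urgently must use the unblinding facility. No change to sample size, visits or analysis is needed.
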